### Eligibility criteria

Eligibility criteria are RRMS, being ≥ 18 years old, and considering immunotherapy for mild/moderate or (highly) active courses. Participants will be excluded if they are diagnosed with SPMS or PPMS, have major cognitive deficits, and/or poor German language skills. Also, prior participation in the development phase of the PExMS website is an exclusion criterion.

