## Methods

### Trial design

The PExMS project follows the guidance of the Medical Research Council [30] for the development and evaluation of complex interventions and adheres to the SPIRIT checklist (see Additional file 1). The process has a development as well as a feasibility and piloting phase.
Development: The PExMS website was developed within a qualitative interview study, where PEx were collected (see ‘Intervention description’).Feasibility and piloting: First, people with RRMS (see ‘Intervention description’) will be asked about their experiences with the PExMS website (e.g. usability, acceptance, layout, navigation) and the outcome measurement procedures.Second, in a two-arm pilot RCT, we will compare a combination of the PExMS website and evidence-based patient information with evidence-based patient information alone. The pilot trial is intended to test recruitment, outcome measures, data collection (sampling and timing), randomisation procedures, and acceptability of the intervention for pwMS and practitioners, and gain exploratory results that could be used for sample size estimations in future RCTs. We want to assess whether the intervention was conducted as intended (fidelity) and assess the quantity of the implemented intervention (dose).A mixed-methods process evaluation will be applied. In the recruitment phase, we will perform semi-structured telephone interviews with all responsible persons in participating centres to assess perceptions of strengths, weaknesses, risks, and opportunities of the study.After completing the study, centres which succeeded in recruitment and centres that dropped out prematurely or failed in recruitment will be interviewed and will be asked to fill out a process evaluation questionnaire to assess acceptability of the recruitment, randomisation and consent procedure, and the intervention itself.Additionally, approximately 10 patients, namely maximum users and minimum users, of the PExMS-website and those having dropped out will be interviewed in each group and will be requested to complete a process evaluation questionnaire.

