**Fig. 1 Fig1:**
[figure not shown]
Flow diagram showing the process of developing a website with PEx

Data for the website was generated in a qualitative interview study with RRMS patients (≥ 18 years old) across Germany. A maximum variation sampling strategy [32] was used aiming to cover experiences with all licensed MS drug treatments. A problem-centred interview guide according to Witzel [33] was applied involving open-ended and closed questions on PEx with diagnosis, talking about MS diagnosis with others, MS in everyday life, and experiences with management approaches (DMT, lifestyle intervention, alternative medicine, rehabilitation) as well as decision-making processes. Interviews were audio- and videotaped, and afterward transcribed. We analysed qualitative data thematically [34] using deductive and inductive categories. All themes representing experiences with MS in everyday life and with therapies were organised in sub-themes and illustrated by text, audio, and video clips to provide the basis for the PExMS-website.

Feasibility testing of the PExMS website will be conducted with people with RRMS (≥ 18 years old) not previously involved in the development phase of the PExMS website. They will receive access to the PExMS website for 1 week for evaluation of the preliminary version of the website. We will record log information (e.g. date, number of logins, and file name of the webpage) by the webserver to assess users’ navigation on the website. Then, two focus group discussions with 5–8 RRMS patients per group will be conducted asking for experiences with the website (e.g. usability, acceptance, layout, navigation) and suggestions for improvement [19]. The focus groups will be audiotaped and transcribed verbatim. Moreover, outcome measures, which are described in the following, will be tested. We will analyse this data descriptively using SPSS Statistics™ Version 25 and use the results for the optimisation of the content and presentation of PEx on the website. The final tool will be used as an intervention in the pilot trial.

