‘Affective forecasting’ is defined as the patient’s perceived ability to make predictions of future feelings about difficult health procedures or disabling health conditions. We hypothesise that PEx could have an impact on patients’ ‘affective forecasting’ [23]. As no validated questionnaire exists for this, a preliminary scale with 5 to 10 items will be developed through a review of relevant literature. We will conduct cognitive interviewing using the think-aloud methodology after showing approximately five patients clips from the website with PEx and the preliminary scale. The clips will show how other patients have coped with emotions during a certain situation as well as the intensity and duration of an emotional state, which the patients experienced. Pilot testing of the revised scale will be conducted applying again cognitive interviewing for face and content validity.

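### As worded, the exclusion rule stops at the development phase, so people who tested the PExMS website and outcome scales in the feasibility phase remain eligible for randomisation, possibly to control

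*Protocol article*

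**What the plan says.** The Trial design section sets up two stages: "The process has a development as well as a feasibility and piloting phase". It identifies the first with the interview work: "The PExMS website was developed within a qualitative interview study, where PEx were collected". The second stage has two steps before the process evaluation. In the first, people with RRMS "will be asked about their experiences with the PExMS website (e.g. usability, acceptance, layout, navigation) and the outcome measurement procedures"; the pilot RCT is the next step.

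The Eligibility criteria for the trial add that "prior participation in the development phase of the PExMS website is an exclusion criterion". No other exclusion concerns earlier contact with the project.

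The text below Fig. 1, in the Intervention description, says more about the testers. They are adults with RRMS "not previously involved in the development phase of the PExMS website". On exposure it says "They will receive access to the PExMS website for 1 week for evaluation of the preliminary version of the website". They then join one of two focus groups of five to eight people. On the scales it adds: "Moreover, outcome measures, which are described in the following, will be tested".

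The Secondary outcomes section describes a separate exercise to build the affective-forecasting scale, in which cognitive interviews take place "after showing approximately five patients clips from the website with PEx and the preliminary scale". The revised scale is then tried in further interviews.

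**The concern.** The rule shows that the authors regard earlier involvement with PExMS as a reason to keep someone out of the trial. As worded, it catches the interviewees who supplied the material but not the people who later used the site and tried the questionnaires. Four things are at stake.

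- **Contrast between arms.** The control is DECIMS-Wiki, described as containing no patient experiences. A former tester allocated to control would bring some exposure to the very component under test.
- **Baseline and blinding.** The Analysis section adjusts for baseline values, but a tester's baseline would follow contact with the site and the scales. The Blinding section relies on describing the study as one of different health information websites. A former tester could recognise PExMS, or notice its absence, and infer the allocation.
- **Feasibility data.** Usage and acceptability are listed among the primary outcomes. Testers would be judging a site that their own suggestions had helped to change.
- **Planning of the main trial.** The Objectives use the pilot's decision self-efficacy difference and its sample-size inputs for the future RCT.

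**Working it through.** The protocol gives no figure for this point that could be reproduced; 55 is a rule-of-thumb total. The check is therefore a comparison of wording, followed by a calculation of scale.

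**Wording**

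1. Trial design: development is the interview study. Website and outcome-measure testing comes under feasibility and piloting.
2. Text below Fig. 1: testers are people with no earlier involvement in the development phase of the website.
3. Eligibility criteria: the excluded group is those who took part in the development phase of the website.

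Items 2 and 3 use the same term for the phase. A person who meets the tester description is, by that description, outside the excluded group when testing starts. Item 1 places the testing itself outside development, so taking part in it does not bring the person under the rule.

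**Inputs for scale**

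- Testers: 2 groups × 5 to 8 people (Intervention description), so 2 × 5 = 10 to 2 × 8 = 16.
- Total sample: 55 (Sample size).
- Allocation: 1:1 (Sequence generation), so about 55/2 = 27.5 controls.
- Number of testers who enrol, m: not stated. It is an assumption, shown over a range starting at 0.

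**Formulas**

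- Expected pre-exposed controls = m/2.
- Share of controls pre-exposed = (m/2)/(55/2) = m/55. If prior exposure carried over in full, the between-arm difference would shrink by this same share. That is a worst case.
- Chance that at least one enrolled tester is allocated to control = 1 − 0.5^m. This treats allocations as independent, which approximates blocked allocation.

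| m enrolled (assumed) | Expected in control | Chance of at least one in control | Shrinkage under full carry-over |
|---|---|---|---|
| 0 | 0 | 0 | 0% |
| 1 | 0.5 | 0.50 | 1/55 = 2% |
| 2 | 1 | 0.75 | 2/55 = 4% |
| 4 | 2 | 0.94 | 4/55 = 7% |
| 10 (all, smaller groups) | 5 | 0.999 | 10/55 = 18% |
| 16 (all, larger groups) | 8 | above 0.999 | 16/55 = 29% |

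The roughly five clip viewers are left out of the table. The protocol does not say whether they are separate from the testers, and a few clips are a smaller exposure than a week on the site.

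**The case against.** The strongest reply is that the authors may have meant the term broadly. The testing paragraph sits under a heading about developing the website. Tester feedback is used to improve the site before it becomes the final tool, and the abstract knows only two steps, development and then the pilot RCT. On that reading everyone involved before the final site is already excluded. This makes a broader intent possible, but it does not override the Trial design section, which assigns testing to the other phase, or the tester description, which uses the rule's own term to set testers apart. Centre staff who apply the rule as written have no basis for turning a tester away.

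Several limits on size stand in full:

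- A reader might add the clip viewers to the testers, reach 15 to 21 people (27% to 38% of 55), and infer contamination on that scale. The documents do not support this. It requires that every one of them enrols and that the two groups do not overlap. Trial participants must also be considering immunotherapy and be recruited at one of two or three centres; nothing says that testers meet either condition.
- A reader might infer that a tester has already received the intervention. Testers have one week of a preliminary version; the intervention is four weeks of the final site together with DECIMS-Wiki. Full carry-over is therefore a ceiling.
- Practice with the questionnaires does not favour either arm in expectation under 1:1 randomisation, and baseline adjustment absorbs part of it. Table 1 shows, however, that PrepDM, social support and eHIQ-Part 2 have no baseline.
- The trial is a pilot with exploratory testing. One or two overlapping participants would move the difference by 2% to 4% at most in expectation, little against the imprecision of a sample of 55.

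**Conclusion.** The gap in the rule is real on the protocol's own wording: testers of the website and scales, and the patients shown clips, are not excluded and can be randomised, possibly to control. What is established is that they are eligible, not that they will take part. The overlap is unknown and may be zero. With a handful of enrolled testers the effect on the estimated difference is small, about 2% for one and 7% for four even under full carry-over; 18% to 29% would need all 10 to 16 to join. The effect on usage, acceptability and baseline data cannot be put in figures from the document, but it points the same way: some participants would not be new to the site or the scales. The problem is modest and avoidable, and worth correcting because the correction is nearly free.

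**What to change.** Extend the exclusion in the Eligibility criteria to prior participation in any earlier PExMS phase, naming the interview study, the website feasibility testing or focus groups, and the testing of the affective-forecasting scale. Alternatively, define the development phase so that it includes these activities, and bring the Trial design section and the tester description into line with that definition. Add one question on earlier PExMS participation to the eligibility screen shown in Table 1.

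The cost is one line of text and one screening question. The total of 55 does not change. At most 10 to 16 testers, plus any separate clip viewers, would be lost as candidates, so the effect on recruitment should be negligible. The Trial status section reports that recruitment had not begun, so the rule could be in place from the first participant.

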## Interventions

### Explanation for the choice of comparators

The control group will receive access to the DECIMS (Decision coaching in MS)-Wiki (www.wiki2.kkn-ms.de), an evidence-based patient information website focusing on MS immunotherapies for 4 weeks. DECIMS-Wiki is considered to provide excellent factual information with figures, but without PEx and is regarded as the gold standard. Further information is described elsewhere [31]. Site visits will be recorded and tracked with the explicit consent of the participants. At the end of the 4-week period, study participants will be invited to complete follow-up questionnaires.

### Intervention description

#### Development of an intervention website with PEx

The intervention is a multimedia PExMS website providing short videos, audio recordings, and written excerpts of 50 pwMS. The development of the intervention followed largely recommendations for standardised qualitative research provided by international DIPEx (Database of Individual Patients’ Experience of illness) association. This collaboration of researchers and health professionals use standardised qualitative research methods to understand PEx and tries to provide ‘balanced’ information from original interview data. However, this project is not affiliated to DIPEx. Figure 1 shows the process of the website’s development.

**Fig. 1 Fig1:**
[figure not shown]
Flow diagram showing the process of developing a website with PEx

Data for the website was generated in a qualitative interview study with RRMS patients (≥ 18 years old) across Germany. A maximum variation sampling strategy [32] was used aiming to cover experiences with all licensed MS drug treatments. A problem-centred interview guide according to Witzel [33] was applied involving open-ended and closed questions on PEx with diagnosis, talking about MS diagnosis with others, MS in everyday life, and experiences with management approaches (DMT, lifestyle intervention, alternative medicine, rehabilitation) as well as decision-making processes. Interviews were audio- and videotaped, and afterward transcribed. We analysed qualitative data thematically [34] using deductive and inductive categories. All themes representing experiences with MS in everyday life and with therapies were organised in sub-themes and illustrated by text, audio, and video clips to provide the basis for the PExMS-website.

Feasibility testing of the PExMS website will be conducted with people with RRMS (≥ 18 years old) not previously involved in the development phase of the PExMS website. They will receive access to the PExMS website for 1 week for evaluation of the preliminary version of the website. We will record log information (e.g. date, number of logins, and file name of the webpage) by the webserver to assess users’ navigation on the website. Then, two focus group discussions with 5–8 RRMS patients per group will be conducted asking for experiences with the website (e.g. usability, acceptance, layout, navigation) and suggestions for improvement [19]. The focus groups will be audiotaped and transcribed verbatim. Moreover, outcome measures, which are described in the following, will be tested. We will analyse this data descriptively using SPSS Statistics™ Version 25 and use the results for the optimisation of the content and presentation of PEx on the website. The final tool will be used as an intervention in the pilot trial.

#### The intervention group

The intervention group will receive access to the PExMS website and the DECIMS-Wiki for 4 weeks. As in the control group, the site visits are tracked. At the end of the 4 weeks, pwMS will be invited to complete follow-up questionnaires.

### Criteria for discontinuing or modifying allocated interventions

Studies investigating PEx as a patient information tool found no adverse events [14, 22, 35]. Therefore, we do not expect any relevant harm of the intervention and did not establish criteria for discontinuing or modifying the allocated intervention for participants. Nevertheless, study participants may withdraw their participation at any time upon request.

### Strategies to improve adherence to interventions

All participating neurological practices, clinics, or rehabilitation centres will receive a study folder including all relevant documents. Also, regular phone calls and telephone conferences will be conducted for arising questions and updates and for sharing experiences.

Usage of the intervention will be monitored by tracking the site visits. PwMS will be contacted by regular email reminders by a member of the coordinating centre to use the intervention. In case of non-use, participants will be reminded by email or telephone.

### Outcomes

#### Primary outcomes

Primary outcomes will be assessed by mixed-methods consisting of interviews and process evaluation questionnaires, which include the following overall feasibility and process-related measures:
Number of participants consented, recruited, randomised, withdrawn, and retainedNumbers with completed outcome measures or lost to follow-upAcceptability of the intervention in terms of frequency and duration of usage as well as experience, motivation, barriers, and facilitators to use the intervention—from the pwMS and participating study centre perspectiveAcceptability of the study procedures in terms of barriers and facilitators to implementation—from the pwMS and participating study centre. We will also ascertain the number and type of adaptations made to implementation strategies including information on how and why.

#### Secondary outcomes

We hypothesise that PEx will lead to a positive effect on decision self-efficacy [23]. This will be assessed by the 11-item ‘Decision Self-Efficacy Scale’ (DSES) [36], which measures self-confidence in decision-making on a five-point-Likert scale. It ranges between 0 (not at all confident) and 4 (very confident). For the total score, items are summed, divided by 11, and multiplied by 25. A total score of 0 means ‘extremely low self-efficacy’, and a score of 100 means ‘extremely high self-efficacy’. The Decision Self-Efficacy Scale shows adequate internal consistency achieving a Cronbach’s alpha of 0.84 [37].

To assess how useful a decision support intervention is in preparing pwMS to communicate at a consultation visit and to make a decision concerning a therapy, the 10-item ‘Preparation for Decision Making’ (PrepDM) [30] scale will be used. It has a five-point-Likert scale format and is designed to be administered after the consultation visit to discuss treatment options. Higher scores show a higher perceived level of preparation for decision-making. Cronbach’s alpha ranges from 0.92 to 0.96 [38].

It is assumed that patients seeing PEx develop greater MS risk knowledge, which we will assess with a short version of the 19-item ‘Risk Knowledge in Relapsing Multiple Sclerosis 2.0’ (RIKNO) [39, 40]. Item difficulty is high ranging from 0.07 to 0.79. RIKNO 2.0 has good internal consistency achieving a Cronbach’s alpha of 0.73 [40].

‘Informed choice’ [41] will be assessed by the Multidimensional Measure of Informed Choice (MMIC) as in previous trials [9, 42]. It comprises three dichotomous dimensions: risk knowledge (good, poor), attitude towards or against immunotherapy or change of immunotherapy (positive, negative), and choice (uptake or non-uptake of the intervention under consideration) leading to eight types of choices. PExMS is expected not to change the percentage of informed choices. Besides, the distribution of decisions made for or against immunotherapy is expected to remain unchanged [22, 35].

The 4-item ‘SURE’ (Sure of myself, Understand information, Risk-benefit ratio, Encouragement) scale [43] addresses decisional conflict in patients. It will assess patients’ perception of uncertainty about decision making for a therapy. The reliability of SURE with a Cronbach’s alpha of 0.54 is moderate [43].

We will assess patients’ preferences for involvement in treatment decisions by the 5-item Control Preferences Scale (CPS) [44]. In a validation study, a Cronbach’s alpha of 0.72 was attained [45].

PEx may give pwMS confidence in active participation and management in medical care [46]. Therefore, the 13-item ‘Patient Activation Measure 13’ (PAM13-D) [47] will be used which is a reliable and valid measure of patient activation with a four-point-Likert scale. It shows good internal consistency achieving a Cronbach’s alpha of 0.87 [47].

The eHealth Impact Questionnaire ‘eHIQ’ [46, 48] measures attitudes of users towards a website which they recently viewed. It is divided into the 11-item eHIQ-Part 1 and the 26-item eHIQ-Part 2. The former represents general attitudes towards using the internet to access health information. The second part is related to the effects of using a specific health-related website on three subscales: (1) confidence and identification, (2) information and presentation, and (3) understanding and motivation. Both answering formats range from 1 ‘strongly disagree’ to 5 ‘strongly agree’. The eHIQ shows good internal consistency achieving a Cronbach’s alpha of ≥ 0.77. A German translation will be validated and used. Moreover, identifying with others who show their experiences on a website, knowing that other pwMS are handling similar problems and learning how they manage difficult issues can reduce the feeling of isolation and improve the sense of social support and group membership [14, 25]. Reformulated items from the subscale ‘confidence and identification’ of the eHIQ will be used to assess social support.

‘Affective forecasting’ is defined as the patient’s perceived ability to make predictions of future feelings about difficult health procedures or disabling health conditions. We hypothesise that PEx could have an impact on patients’ ‘affective forecasting’ [23]. As no validated questionnaire exists for this, a preliminary scale with 5 to 10 items will be developed through a review of relevant literature. We will conduct cognitive interviewing using the think-aloud methodology after showing approximately five patients clips from the website with PEx and the preliminary scale. The clips will show how other patients have coped with emotions during a certain situation as well as the intensity and duration of an emotional state, which the patients experienced. Pilot testing of the revised scale will be conducted applying again cognitive interviewing for face and content validity.

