## Objectives

By embedding a process evaluation within the pilot trial, the primary study objective is to test the feasibility of an intervention using PEx as a supplement to evidence-based information to establish whether it is possible to carry out a large future RCT. The specific objectives are to determine the following:
Acceptability of recruitment, randomisation, and consent procedureAcceptability and feasibility of collecting reliable and valid data on primary and secondary outcomesAcceptability of the intervention and processes to participants and clinical staffSuitability of the intervention usedBarriers to adherenceExplore aspects of the trial design and conduct with a patient and public involvement group

We hypothesise that PEx may help pwMS in the decision-making process for or against immunotherapy or their different forms, respectively. Therefore, the secondary objectives are (1) to obtain pilot data on the likely difference between the intervention and evidence-based information alone regarding decision self-efficacy; (2) to inform the sample size calculation for the substantive randomised clinical trial; and (3) to control for potential bias caused by PExMS.

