### Sample size

To our knowledge, there is no previous research using decision aids with patient narratives and addressing decision self-efficacy. However, since the main aim of the pilot RCT is not to give a formal assessment of efficacy, but rather to evaluate trial procedures and processes as well as to get estimates of parameters for the main RCT sample, the sample size justification is based on rules of thumb for pilot RCTs as given by Sim and Lewis. The authors recommend for a two-armed pilot RCT a total sample size of 55, which would minimise the overall sample size for the main RCT for small to medium standardised effect sizes [52–54]. Additionally, pilot RCTs on decision support tools in MS showed comparable sample sizes [31, 55].

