## Analysis

The feasibility and process evaluation findings will inform the design of a future fully powered, randomised controlled trial to formally evaluate the effectiveness of the intervention. Therefore, we seek a drop-out rate < 20% and to collect > 60% of patient-reported outcomes (questionnaire response rate). Frequencies will be determined for categorical variables, and summary statistics (mean and standard deviation or median and quartiles, as appropriate) will be calculated for quantitative variables. Exploratory formal hypothesis testing using ANCOVA models will be performed since this is a pilot RCT. Estimated differences in outcome measures of efficacy adjusted for baseline values will be calculated. No interim analyses and stopping guidelines are planned. Initially, all analyses will be performed on complete cases. If necessary, sensitivity analyses will be conducted with imputed datasets derived by multiple imputation or mean value imputation.

Qualitative data gained through interviews will be managed using MAXQDA Analytics Pro 2018 and analysed thematically following Braun and Clarke [34].

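### Attitude to immunotherapy is described only as positive/negative inside the informed-choice measure; a baseline-adjusted graded score would be a more precise supporting check on bias

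*Protocol article*

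**What the plan says.** The Objectives section of the protocol article gives, as the third secondary objective, "to control for potential bias caused by PExMS". It attaches no measure to that objective.

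Under Secondary outcomes, attitude appears as one part of the MMIC: "It comprises three dichotomous dimensions: risk knowledge (good, poor), attitude towards or against immunotherapy or change of immunotherapy (positive, negative"; choice (uptake or not) is the remaining dimension. Two expectations of no change follow: "PExMS is expected not to change the percentage of informed choices", and "the distribution of decisions made for or against immunotherapy is expected to remain unchanged". Neither has a margin. Risk knowledge, another MMIC dimension, also has its own outcome in the RIKNO questionnaire. Attitude to immunotherapy has none; the attitudes in the eHIQ are towards websites.

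Table 1 places the MMIC at baseline and at t1, after 4 weeks of website use. The treatment decision is recorded at t2, after the physician encounter.

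The Analysis section plans exploratory ANCOVA and adds: "Estimated differences in outcome measures of efficacy adjusted for baseline values will be calculated". It does not name attitude. The Sample size section settles on 55 patients and says that "the sample size justification is based on rules of thumb for pilot RCTs".

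**The concern.** A positive/negative split records only whether a patient crosses the cut. A patient who moves from mildly to strongly in favour, or the reverse, counts as unchanged. Everyone enrolled is already considering immunotherapy, so many may start on the positive side (the article gives no figure), and a shift towards treatment would then show poorly.

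Attitude is worth measuring well because of its timing. It is scheduled before and directly after website use, whereas the recorded decision also reflects the consultation. With so few patients, a coarse summary of attitude will often show no difference even if the stories have moved attitudes moderately. That could be taken as some reassurance about bias when the main trial is designed. Patients are scarce in a pilot, which is a reason to use the information each one gives.

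**Working it through.** **The plan's own figure.** The sample size of 55 is a cited rule of thumb without alpha, power, SD or effect size. It can be neither reproduced nor shown wrong, and it is not in dispute.

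**Inputs from the article.** Total 55, allocation 1:1, taken here as 28 control and 27 intervention; drop-out target below 20%.

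**Assumptions.** Two-sided 5%; a normal graded attitude behind the split; a shift of d = 0.5 SD; control share positive p0 of 50%, 70% or 80%; baseline correlation r = 0.5.

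**Graded score, unadjusted.** Noncentral t with 53 degrees of freedom and noncentrality d × √(28 × 27/55) = 0.5 × 3.71 = 1.85. Power is 44%.

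**Graded score, ANCOVA.** The effect becomes d/√(1 − r²) = 0.5/√0.75 = 0.577, with noncentrality 0.577 × 3.71 = 2.14. Power is 56%.

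**After the cut.** The intervention share is p1 = Φ(Φ⁻¹(p0) ± 0.5). Power is the sum of the exact binomial probabilities of all outcomes for which the uncorrected chi-square test is significant.

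| Control positive | Shift | Intervention positive | Power |
|---|---|---|---|
| 50% | up (down is the mirror image) | 69% | 31% |
| 70% | up | 85% | 26% |
| 70% | down | 51% | 32% |
| 80% | up | 91% | 23% |
| 80% | down | 63% | 27% |

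The range is 23–32%. If the intervention arm has 28 patients and control 27, it is 21–33%; a normal approximation with 27.5 per arm gives 21–30%. Like for like, without baseline adjustment, the loss is 44 − 32 = 12 to 44 − 23 = 21 percentage points.

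**Information kept.** For a cut at p0, the efficiency is φ(z)²/[p0(1 − p0)], with z = Φ⁻¹(p0): 0.64, 0.58 and 0.49 at 50%, 70% and 80%. The 55 patients then act like 55 × 0.64 = 35, 55 × 0.58 = 32 or 55 × 0.49 = 27.

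**Interval widths.** The 95% half-width for a difference in share positive is 1.96 × √[p(1 − p)(1/28 + 1/27)] = 26, 24 or 21 percentage points. For the graded score it is 1.96 × √(1/28 + 1/27) = 0.53 SD, or 0.53 × √0.75 = 0.46 SD with ANCOVA.

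**Limits of the gain.** If 20% drop out (44 analysed), unadjusted power at 0.5 SD is about 37% graded and 18–25% after the cut. At 0.2 SD, every version is weak: 13% with ANCOVA against 8–10% after an upward shift across the cut.

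**The case against.** The strongest reply is that the article states how the MMIC classifies patients. It does not say how attitude is answered, or that the split is the only analysis. A condensed article may leave scoring to the full protocol or SAP, and the Analysis section does not exclude a graded score: its ANCOVA sentence is not confined to efficacy measures. This stands, and it is why the power figures are conditional and the recommendation covers both a graded and a yes/no item.

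It is also fair that the pilot claims no power. The article says that "the main aim of the pilot RCT is not to give a formal assessment of efficacy", calls its testing exploratory, and nowhere says that a non-significant result would be read as no change. A graded score would still miss a 0.5 SD shift about as often as not, so the small sample is as much a cause of the low sensitivity as the cut. This stands too, and it makes the change an improvement in precision, not the repair of a wrong figure.

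A reader might infer more: that the whole bias objective loses its sensitivity because attitude is the most direct sign of persuasion. The documents do not support that. The objective names no measure, and the stated no-change expectations concern informed choice and the decision made. The decision is categorical by nature and at least arguably as direct. A reader might also set 56% against the post-cut figures and credit the whole gap to undoing the cut. That mixes two changes, because the ANCOVA figure includes baseline adjustment, and baseline MMIC data could be used to adjust a binary analysis as well.

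**Conclusion.** The point holds for the attitude component. As described, attitude to immunotherapy enters only as positive/negative, it is scheduled at two useful times, and no other outcome carries it. Under the stated assumptions the cut costs about 12–21 points of unadjusted power at a 0.5 SD shift (44% down to 23–32%) and 36–51% of the information. Baseline adjustment of a graded score would add about 11 points (44.4% to 55.6%) at r = 0.5.

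The size rests on a graded normal attitude, the control share positive, the correlation and the shift, none of which the article gives. The finding does not show that the bias objective as a whole fails, and a graded score would leave the pilot imprecise, with a half-width near half an SD.

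**What to change.** Keep the MMIC classification and the decision outcome as they are. Under Secondary outcomes and Analysis, add the attitude score on its full response scale at t1, with the adjusted mean difference between arms and its 95% CI from the ANCOVA already planned (baseline attitude as covariate). Label it a supporting exploratory check under the third secondary objective, and not the main one. State that it will be interpreted by what the interval includes, so that non-significance is not read as absence of bias. In Objectives, name the measures that serve this objective.

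If the attitude item is at present a yes/no answer, collect a graded response and derive the positive/negative split from it.

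The cost is one further exploratory analysis of a measure already scheduled at baseline and t1, with no added visits or patients. A yes/no item would also need a small change of response format to an instrument taken over from previous trials, which could make comparison with them less direct. The article reports that recruitment had not begun, so the change could precede it.
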